#### Composition of the data monitoring committee, its role, and reporting structure {21a}

There will not be a data monitoring committee as the treatments under consideration are regarded as safe methods.

#### Adverse event reporting and harms {22}

When applied following established safety protocols, tDCS is regarded as a safe method of brain stimulation, causing no apparent short- or long-term harm [42]. The effects and risks of tDCS are limited by safety protocols that limit the applied current, duration, and frequency of stimulation sessions [66]. The parameters used in this trial are within the safety guidelines; therefore, adverse effects are minimized. At the end of every tDCS session, the participants will be asked whether they experienced any adverse effects (e.g., headaches, itching, tingling, burning), how severe possible adverse effects were (from very mild to severe), and whether they relate the adverse effect to the stimulation as recommended by Aparicio et al. [67].

All adverse events, whether or not considered related to the cognitive remediation training or tDCS, that are reported by the participant or observed by the investigators or health professionals, will be recorded from the time a participant consents to join the trial until the last trial visit. The adverse events will be assessed for seriousness and will be reported to relevant regulatory bodies.

#### Frequency and plans for auditing trial conduct {23}

No formal, external audit will be conducted. The project management group will meet bi-weekly to review the trial conduct, enrollment rates, and to oversee and conduct the study in general. In monthly meetings of the project management group, BC, and GM, the conduct and progress of the study will be discussed.

#### Plans for communicating important protocol amendments to relevant parties (e.g., trial participants, ethical committees) {25}

Important protocol modifications which may have an impact on the conduct of the study, the potential benefit for the participant, or may affect participant safety will be communicated to the trial participants, trial registries, the Ethical Committee, and the sponsor. Minor corrections or clarifications of the protocol that have no effect on the way the study is conducted will be documented in a list of amendments.

### Dissemination plans {31a}

The results of this pilot study will be publicly disclosed. Presentations of the results will be given at (inter-)national conferences. Moreover, the results will be published in an international scientific journal, as well as in a Dutch journal to reach more clinicians in the field.

## Discussion

Impaired cognitive functioning in SMI is related to a higher level of dependency on mental health care [13], as well as lower levels of daily [12], community [15], and occupational functioning [16]. Hence, interventions that aim to improve cognitive functioning are needed to foster recovery. The presented trial will help to elucidate whether the addition of innovative cognitive enhancement interventions to treatment as usual can lead to clinically relevant improvements in the daily functioning of service users dependent on residential facilities and whether these improvements can be retained beyond the treatment period.

This study differs from previous trials in that it investigates the effects, the feasibility, and acceptability of a CR program that incorporates all four core elements of CR as defined by Bowie et al. [25], in a population with severe mental illness dependent on long-term support in a clinical or sheltered setting, which has not been done before. While some trials investigated the efficacy of cognitive training in inpatients with psychosis [20], none of the administered programs included all four core components of CR. These cognitive training approaches in inpatients with schizophrenia were effective in improving cognitive functioning, but not daily functioning. As CR has shown the potential to provide benefits in both cognitive and daily functioning in people with schizophrenia [18, 19], these CR programs may also enhance daily functioning in people with SMI.

Additionally, this trial combines cognitive remediation with non-invasive brain stimulation. Previous trials focused mainly on combining tDCS with cognitive training approaches that were based on an independent, repetitive, drill, and practice approach. The improvement achieved by this independent approach is not only limited to cognitive functioning when used as stand-alone treatment [24] but also when used in combination with non-invasive brain stimulation ([name] et al., in preparation). To our knowledge, this trial is the first to combine tDCS with CR program in a psychiatric population.

In the presented trial, a multiple baseline randomized controlled design is used. This trial design has several advantages. Firstly, prior research has demonstrated the efficacy of the CR program used in this trial [26, 27]. In the multiple baseline design, every participant can be exposed to the intervention. The use of this design is, therefore, more ethical than a traditional randomized controlled trial, in which individuals in control groups are not exposed to the intervention of interest.

Secondly, the 4-month waiting period serves as a control condition and allows investigating the effects within individuals. A within-subject analysis is more informative than group comparisons in this trial, as individual differences in various domains can influence the efficacy of the treatment: for example, the cognitive deficits experienced, which may occur within different cognitive domains [68]; and physiological factors related to the current flow of tDCS such as skull thickness, subcutaneous fat levels, cerebrospinal fluid density, and cortical surface topography [69]. Using within-subject analyses allows determining whether the intervention is superior to treatment as usual for each individual. If the intervention appears to be more effective for some individuals than for others, then the differences between those individuals can be further investigated.

However, the use of a multiple baseline design has some disadvantages and challenges. Firstly, the assessments happen over a period of time and the control condition will, on average, contribute data from an earlier calendar time. Therefore, time effects could influence the results. However, psychiatric symptoms and cognitive impairments are generally stable in the targeted inpatient population, which minimizes the risk of time effects. A second challenge arising due to the presence of a waiting period is that participants might become less engaged during the waiting period and drop out before the intervention has started. Thus, it will be important to keep regular contact with the participants during the waiting period. The therapist will contact all participants once a month, to keep the engagement process as similar as possible across the whole group. While keeping the participants engaged may be a challenge, the contact moments allow building up a therapeutic relationship with the participant which could relate to higher motivation during the intervention. Thirdly, as all participants receive CR, the investigators, the therapist, and the participants are not blind to whether or not participants receive CR. To control for possible influences of this disadvantage to the assessments, assessors will be kept blind to the intervention conditions by not disclosing the study aims and design to them.

Another challenge in this trial is the evaluation of the superiority of adding active tDCS to the cognitive remediation over sham tDCS. Active tDCS will be added to the treatment of only half of the participants, and the efficacy will be analyzed in a group analysis. The chosen study design requires fewer participants than a traditional randomized controlled trial to investigate the CR efficacy given the within-subject comparison. Yet, because of the small sample size and the expectation that CR on its own can improve cognitive and daily functioning, the power to detect significant differences between the groups with respect to tDCS efficacy is low. While statistical significance may be difficult to achieve, this pilot study can at a minimum identify a trend towards superior treatment effects of combined CR and tDCS as compared to CR only. If the addition of tDCS seems to have an additive effect on CR, we aim to initiate a multicenter randomized controlled trial to further investigate the efficacy.

In summary, this pilot trial could offer new insights into the possibility of improving cognitive functioning in people with severe mental illness. The use of a waitlist control condition enables us to investigate the clinical relevance of cognitive enhancement interventions in the heterogeneous population of people with SMI. Moreover, this trial may contribute to the discovery of new interventions that foster the functional recovery of service users living in long-stay clinical facilities.

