#### Secondary objective

The secondary objective of this pilot study is to assess whether adding prefrontal tDCS to CT is feasible and acceptable. Furthermore, we aim for an indication of a potential additional effect of the combined intervention on cognitive performance and daily functioning compared to CR + sham tDCS.

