### Trial design {8}

The trial is designed as a pragmatic, randomized, controlled, pilot trial following a non-concurrent multiple baseline design with the participants serving as their own control. Participants will be randomized over two conditions: CR + sham tDCS (group 1) or CR + active tDCS (group 2) with a 1:1 allocation ratio, see Fig. 1. The trial will start with a waiting period of 16 weeks for all participants, which serves as a within-subject control condition, and is followed by the allocation of the participants to one of the treatment groups. During the next 16 weeks, the participants will receive 32 sessions of the allocated intervention. The participants will be invited back for a follow-up measurement 6 months post-treatment. In case of positive indications, we will extend the trial into a multicenter trial using the same design and recruit more participants.

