### Sample size {14}

For this pilot trial, the sample size is based on Whitehead et al. [56], who evaluated and compared methods for sample size calculation for pilot studies in order to minimize the recruitment of participants across pilot and main trial while maintaining the average power. The authors advise a pilot sample size of 10 participants per treatment arm if the estimated standardized effect size of the main trial is medium or large. We estimated a medium effect size based on the results of a large meta-analysis that demonstrated moderate effects of CR on cognition (effect size 0.45) and daily functioning (effect size 0.42) [18]. Taking into account a drop-out percentage of 20%, a total of 26 participants are required in order to reach a sample size of 10 participants who complete the trial per treatment arm. By considering the pilot study as a part of the main trial, this method allows to include the pilot data, if the trial is extended to a large randomized trial with a similar design.

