##### CR vs. treatment as usual

The mean differences in outcomes of both groups combined will be compared to the waitlist period using multilevel modeling to assess the effect of CR over treatment as usual. A two-level model will be built with subject (level 2) and time point of assessment (level 1) entered as levels. The significance of the fixed regression effects is tested using the appropriate *t-*test (*α* = .05).

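### The Discussion assures readers that the pilot can at least identify a trend favouring added tDCS and links a further trial to an apparent additive effect; 10 to 13 per arm cannot support that assurance

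*Protocol article*

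**What the plan says.** The effect of tDCS sits under the secondary objective, after feasibility and acceptability, and is framed modestly: "we aim for an indication of a potential additional effect of the combined intervention on cognitive performance and daily functioning compared to CR + sham tDCS". The Discussion section goes further. It concedes that power for the tDCS comparison is low because the sample is small and both arms receive CR. It then states that "this pilot study can at a minimum identify a trend towards superior treatment effects of combined CR and tDCS as compared to CR only", and continues: "If the addition of tDCS seems to have an additive effect on CR, we aim to initiate a multicenter randomized controlled trial". Neither sentence names an outcome, a time point or a threshold.

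Two other places describe what follows the pilot. The Abstract (Discussion paragraph) says the pilot will be extended to a large multicentre study if CR improves cognition, irrespective of whether tDCS adds anything. Trial design {8} makes extension conditional only on positive indications, without saying of what.

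On size, Sample size {14} relies on a published rule: "The authors advise a pilot sample size of 10 participants per treatment arm". It then says "Taking into account a drop-out percentage of 20%, a total of 26 participants are required". The only effect sizes given are those of CR itself: "moderate effects of CR on cognition (effect size 0.45) and daily functioning (effect size 0.42". None is given for tDCS added to CR.

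**The concern.** The claim is worded as a floor: whatever else fails, a trend will be identifiable. That is a statement about how the design behaves, so it can be checked. If it is wrong, a reader of the results may take a favourable difference as support for tDCS when chance alone would often produce one. A reader may equally take an unfavourable difference as evidence against a combination that works. The next sentence of the Discussion attaches a decision to that impression, and other sections describe the decision differently. It is then unclear which result would lead to which next step.

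**Working it through.** **The plan's own figure.** 10 completers / (1 - 0.20) = 12.5, rounded up to 13 per arm, 26 in total. This reproduces. The 10 per arm is a rule of thumb for pilots, not a power calculation for tDCS, and no power for that contrast is stated.

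**Inputs.** n = 10 completers or 13 randomised per arm, 1:1 (Sample size {14}, Trial design {8}). True tDCS effect d in SD units: 0, 0.2 and 0.45. The 0.2 is an assumption. The 0.45 is the document's figure for CR as a whole, borrowed here for an add-on. A baseline correlation of 0.7 for the adjusted case is also an assumption.

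**Precision.** SE = sqrt(2/n): 0.447 for n = 10, 0.392 for n = 13. The 95% half-width is t × SE: 2.10 × 0.447 = 0.94 SD and 2.06 × 0.392 = 0.81 SD. Baseline adjustment multiplies the SE by sqrt(1 - 0.7²) = 0.714, giving 0.319 and 0.280, with half-widths of about 0.67 and 0.58 SD.

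**Conventional power.** For d = 0.45 at two-sided 0.05 (noncentral t, unadjusted) power is 16% and 20%, which agrees with the plan's admission that it is low. The tDCS analysis section states no alpha. The 0.05 is stated for CR versus treatment as usual, and two-sided is assumed.

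**Reading A: a trend is a favourable sign on one outcome.** P(wrong sign) = Φ(-d/SE). For example, n = 10 and d = 0.2 gives Φ(-0.447) = 0.327. With d = 0 the favourable sign appears in 50% of trials, whatever n is.

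**Reading B: a trend is two-sided p<0.10 in favour of active tDCS.** P(trend) comes from the noncentral t with 2n - 2 degrees of freedom and noncentrality d × sqrt(n/2). With d = 0 this is 5%.

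| Result | n = 10 | n = 13 |
|---|---|---|
| A: false trend, d = 0 | 50% | 50% |
| A: wrong sign, d = 0.2 | 33% | 31% |
| A: wrong sign, d = 0.45 | 16% | 13% |
| A, adjusted: wrong sign, d = 0.2 | 27% | 24% |
| A, adjusted: wrong sign, d = 0.45 | 8% | 5% |
| B: false trend, d = 0 | 5% | 5% |
| B: missed, d = 0.2 | 89% | 88% |
| B: missed, d = 0.45 | 75% | 70% |
| B, adjusted: missed, d = 0.2 | 85% | 83% |
| B, adjusted: missed, d = 0.45 | 61% | 53% |

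**More than one outcome.** The tDCS comparison uses the same measures as the primary outcomes, at least nine of them. Taking eight and no true effect, at least one favours active tDCS in 1 - 0.5^8 = 99.6% of trials if they are independent, and in about 89% if they correlate at 0.5.

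**Progression statements side by side.** Abstract: extend on a CR benefit, with or without a tDCS benefit. Trial design {8}: extend on unspecified positive indications. Discussion: a multicentre trial is aimed for if tDCS appears additive. A result with a CR benefit and no apparent tDCS benefit leads to extension under the first, while the third gives no ground for a further trial.

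**The case against.** The strongest reply is that the plan is already candid. The same paragraph says power is low and significance unlikely, and the objective speaks only of an indication. The sentence is also Discussion prose in a condensed article, not a formal progression rule. All of that stands, and it limits the weight of the point. It does not rescue the assurance itself: a threshold for a trend kept in an unseen analysis plan would choose between the two kinds of error, not remove both.

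A second reply is that the unadjusted figures are pessimistic. The plan has two pre-treatment and two post-treatment assessments in a multilevel model, analyses by intention to treat, and invites those who drop out back for assessment. That is fair, and the adjusted rows allow for it in part. At 0.45 SD with adjustment the sign is right in 92-95% of trials, so the sign is not a coin toss for an effect that large. For smaller increments, or under the p<0.10 reading, the error rates stay high.

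Three stronger readings are tempting and are not supported:

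- A reader might infer that the small sample causes a false trend half the time and also causes useful effects to be mostly missed. The 50% belongs to the sign reading and holds at any sample size. The 70-89% miss rates belong to the p<0.10 reading, where the false rate is 5%. The two cannot be joined.
- A reader might infer that the whole follow-on programme hangs on the tDCS trend, so that an unfavourable sign would end work on the combination. The Abstract says otherwise, and Trial design {8} says an extension would keep the same design, which includes both tDCS arms. Only the Discussion makes the link.
- A reader might infer that the secondary objective is to be answered by the sign of a difference. The objective puts feasibility and acceptability first, and the statistical section plans a model-based comparison of mean differences. No section says that the sign decides.

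**Conclusion.** The point holds as a misstated property of the design, together with progression statements that do not agree. It is not a fault in the sample size as such: 26 follows from the rule the plan cites, and low power for tDCS is disclosed. Under either reading of a trend that was tested, at least one error rate is too high for a guaranteed minimum: 50% false trends under the sign reading, or 70-89% missed effects (53-85% adjusted) under p<0.10. The false-trend rates depend on the definition of a trend and not on an effect size. The wrong-sign and miss rates rest on assumed tDCS effects of 0.2 to 0.45 SD, and the adjusted figures on an assumed baseline correlation of 0.7. The documents give neither.

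**What to change.** 1. In the Discussion, delete the claim that the pilot can at least identify a trend.
2. State instead that the active versus sham contrast will be reported as an estimate with its 95% confidence interval (expected half-width roughly 0.6 to 0.9 SD), and that neither its sign nor a trend will be used to infer superiority or to decide on a further tDCS trial.
3. Base tDCS progression on the feasibility and acceptability results already planned: the retention and session thresholds under Feasibility, and the post-intervention interview under Acceptability and Acceptability of tDCS.
4. Reconcile the Discussion with the Abstract and Trial design {8}, so that one statement says what follows the pilot and on which result.

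One substitute should be avoided: proceeding if the confidence interval still includes a worthwhile increment. With no true effect and an assumed increment of 0.45 SD, the upper limit reaches it in 1 - Φ((0.45 - 0.94)/0.447) = 86% of trials at n = 10 and 1 - Φ((0.45 - 0.81)/0.392) = 82% at n = 13. Such an interval is not positive evidence. At most, an interval that excludes the increment could be noted as evidence against.

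The cost is a rewritten paragraph and one consistent progression statement, with no extra participants. The article reports recruitment as ongoing and keeps the allocation sealed until all follow-up is complete, so the change can be made before any unblinded result. The downside is a more modest stated claim.

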### Trial status

Recruitment is currently ongoing. Participant enrollment started in October 2020 and will continue until 26 participants are included in the study. The predicted recruitment end date is 31 December 2021.

## Abbreviations

CFQ: Cognitive Failure Questionnaire
CIRCuiTS: Computerized Individualized Remediation of Cognition and Thinking Skills
COWAT: Controlled Oral Word Association Test
CR: Cognitive remediation
CREW: Cognitive Remediation Expert Working Group
DLPFC: Dorsolateral prefrontal cortex
LSP: Life skills profile
MATRICS: Measurement and Treatment Research to Improve Cognition in Schizophrenia
MCST: Modified Card Sorting Test
NOSCA: Nurses’ Observational Scale of Cognitive Abilities
PANSS: The Positive and Negative Syndrome Scale
RCFT: Rey Complex Figure Test
SMI: Severe mental illness
SNS: Self-evaluation of Negative Symptoms
tDCS: Transcranial direct current stimulation
WAIS-IV: Wechsler adult intelligence scale IV
WT-15: 15-word learning task
